### Randomization, blinding, and allocation concealment

We will screen 75 patients in strict accordance with the inclusion or exclusion criteria and then randomly divide them into three groups by computer-assisted block randomization stratified by disease severity. The random grouping will be performed by independent individuals who are not involved in the recruitment process. Sealed opaque envelopes will be used to conceal the patient distribution. Given the nature of the study, neither the intervention practitioner nor the participant can be blinded to the treatment plan, so blinding is only applicable for the data collection and evaluation. Neither patients nor the public will be involved in the design, conduct, reporting, or dissemination plans of our research. An illustration is shown in Fig. 2, and the time points are shown in Table 1.

**Fig. 2 Fig2:**
[figure not shown]
Profile of our research

### Data collection, management, and analysis

All patients’ data will be recorded by trained clinical researchers using a standardized case report form (CRF) and saved using the EpiData electronic database. To ensure the reliability of our study, the management of this trial will be conducted by the Trial Steering Committee (TSC). Main investigators and statisticians consist of our Trial Steering Committee, who will oversee the entire trial. Meetings will be held once a month to monitor the progress of the research and to share opinions when there are problems. The measurement data will be expressed by mean ± SD, and the count data will be expressed by frequency and percentage. A Kolmogorov-Smirnov test will be performed to analyze sample normality. Within-group changes in sputum viscosity, FEV_1_%, vital capacity, arterial oxygen saturation, quality of life, and the level of anxiety will be compared using a paired *t*-test or Wilcoxon test depending on the data distribution. Inter-group differences between baseline and post-intervention among the outcomes will be compared by one-way analysis of variance. According to the normality of the data distribution, a general linear model or multi-generalized linear model will be used to compare the differences between the primary and secondary outcomes after adjusting the covariates, including sociodemographic variables, such as sex, age, body mass index, smoking history, severity of disease, among others, and baseline variables. In addition, we will follow the principle of intention to treat (ITT) and use the sequence mean method to deal with the missing data to analyze the results of the comparison between groups of each outcome. To assess whether the missing data will affect the results of the study, we will compare participants who did not complete the intervention with those who completed the intervention to verify the sensitivity of the results of the trial. A two-tailed *p*-value of < 0.05 will be taken as significant. The data from this experiment will be entered by Epidata3.1 and analyzed by SPSS 26.0 software.

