## Methods

### Study design

This is a single-blind, three-arm, randomized controlled trial. The intervention group will receive active cycle of breathing techniques combined with phonophoresis and control group 1 will receive active cycle of breathing only, while control group 2 will receive phonophoresis only. By comparing these three groups, we hope to explore the benefits of a combined program, compared to a single intervention. For the three-armed trial [26], COPD patients will receive active cycle of breathing techniques during hospitalization. Because the mean length of hospital stay for COPD patients in our medical center is 1 week, the duration of the intervention in our study will be set at 1 week. The trial will be conducted at the Medical Center in Changchun, China. In line with the recommendations of the Protocol Items Recommendations for Interventional Trials (SPIRIT) guidelines [27], our research protocol has been registered with the China Clinical Trial Registration (ChiCTR1900028506) and has been approved by the Ethics Committee of Jilin University (2019122301). We expect to begin recruitment in December 2019 and end in June 2021. Any changes to the plan will be negotiated with trial participants and the ethics committee. A copy of the revised protocol will be sent to the patient involvement branch of the ethics committee to add to the Investigator Site File, and any deviations from the protocol will be fully documented using a breach report form.

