### Sample size

Since the trial was designed with three arms, analysis of variance was chosen to calculate the sample size. We will have 90% power at the significance level (alpha) of 0.15 with an effect size of 0.4 to detect significant differences in sputum viscosity. Based on previous studies [45, 46], we assume that the dropout rate of our trial will be about 20% after the week-long intervention. Thus, the total sample size was 75, with 25 patients in each of the three groups. The sample size was calculated using the software PASS 2019.

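### The between-group test is an omnibus one-way ANOVA that does not answer whether the combination beats a single treatment, and the adjusted model planned beside it is not ranked against it

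*Protocol article*

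**What the plan says.** All references are to the protocol article.

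- **Aim (Study design):** "By comparing these three groups, we hope to explore the benefits of a combined program, compared to a single intervention". The Introduction likewise expects the combination to do more than one treatment alone.
- **Between-group test (Data collection, management, and analysis):** "Inter-group differences between baseline and post-intervention among the outcomes will be compared by one-way analysis of variance". The Abstract also names only analysis of variance for group differences.
- **Sizing (Sample size):** "Since the trial was designed with three arms, analysis of variance was chosen to calculate the sample size". The stated inputs are alpha 0.15, 90% power, effect size 0.4 and 20% dropout, giving 75 patients, 25 per arm. The analysis section uses two-tailed 0.05.
- **Second between-group analysis (same section as the test):** "a general linear model or multi-generalized linear model will be used to compare the differences between the primary and secondary outcomes after adjusting the covariates". Normality of the data decides between the model families. The covariates are given as "such as sex, age, body mass index, smoking history, severity of disease, among others, and baseline variables".
- **Randomisation:** "computer-assisted block randomization stratified by disease severity". The stratifier therefore appears among the covariates of the second analysis.

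The text does not say which of the two analyses is decisive, and it ties neither to the comparison of the combination with each single treatment.

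**The concern.** The aim implies two directed comparisons: combination against breathing technique, and combination against phonophoresis. A three-group F test with 2 numerator degrees of freedom responds to any spread among the means. It gives the same answer whether the combination is best, worst or in between. Followed literally, the plan can return a significant result that says nothing in favour of the combination. The two single-treatment arms could well differ, since one gets supervised airway clearance with inhaled mucolytics and the other gets phonophoresis.

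The second problem is choice. There are two between-group analyses with no ranking, a covariate list without an end, and a model family picked from the trial's own data. Together these leave room to select the favourable result after the data are seen.

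**Working it through.** **Inputs.** From the document: three equal arms, 75 randomised, 20% dropout, effect size 0.4, alpha 0.15 (Sample size), two-tailed 0.05 (analysis). Assumed: 0.4 is Cohen's f, which the first step supports.

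**1. The plan's own figure.** The noncentrality is λ = N f². With 20 evaluable per arm, λ = 60 × 0.16 = 9.6 on 2 and 57 degrees of freedom. At alpha 0.15 power is 0.905, and 60 / 0.8 = 75. The stated 75 is reproduced exactly, as an omnibus ANOVA. At the analysis level of 0.05 the same design has omnibus power 0.776.

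**2. Patterns of means with the same f.** f is the SD of the three means divided by the within-group SD.

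- One arm apart by d, the other two equal: the SD of the means is d√2/3, so d = 0.4 × 3/√2 = 0.849 SD.
- Evenly spaced by h: the SD of the means is h√(2/3), so h = 0.4 × √1.5 = 0.490 SD.

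**3. Simulation.** 20 per arm, two-sided 0.05, pairwise t tests with the pooled variance. Means are listed as combination, breathing technique, phonophoresis; higher is better.

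| True pattern (SD) | F significant | Beats both | F significant, beats neither |
|---|---|---|---|
| Combination best, controls equal (0.849, 0, 0) | 78% | 62% | <0.1% |
| Evenly spaced, combination best (0.98, 0.49, 0) | 78% | 32% | 0.4% |
| Combination = breathing technique > phonophoresis (0.849, 0.849, 0) | 78% | 2.5% | 8% |
| Combination midway (0.49, 0.98, 0) | 78% | <0.1% | 45% |
| Combination worst (0, 0.849, 0.849) | 78% | 0% | 78% |

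The first column does not move, because F depends only on the spread of the means.

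**4. Power of one contrast.** In the first pattern the noncentrality is 0.849 × √(20/2) = 2.68 on 57 degrees of freedom, which gives power of about 75%. For 90% power per contrast, 30 evaluable per arm are needed: 90 in total, and 90 / 0.8 = 112.5, so 113 with dropout. This is 90% for each contrast, not for both together.

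**5. Gain from baseline adjustment.** Assume equal baseline and follow-up variance σ² and correlation r. The change score has variance 2(1 − r)σ² and ANCOVA has residual variance (1 − r²)σ². The ratio is (1 + r)/2: 0.65, 0.75 and 0.85 for r = 0.3, 0.5 and 0.7. The document gives no r.

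**The case against.** - **A reader might infer that the plan ignores baseline and the stratifier.** The document does not support that. The ANOVA appears to be on change from baseline, so baseline enters as a change score. The next sentence plans a model adjusted for severity of disease and baseline variables. What stands is that the ANOVA adjusts for neither as a covariate, and that the model that does is not declared decisive.
- **A reader might take 78% against 2.5% to mean that the combination beats neither single treatment.** It does not. In that pattern the combination is truly better than phonophoresis and shows it in about 75% of trials. The 2.5% is the ordinary one-directional error rate for a contrast with no true difference. The case of beating neither is shown by the midway pattern (45%) and the worst-arm pattern (78%).
- **No rule in the article equates a significant F with success for the combination, and none requires it to beat both single treatments.** That is correct; the both-must-win rule below is a recommendation. An omnibus test followed by pairwise tests is also ordinary three-arm practice, and pairwise detail may sit in an analysis plan not shown. Its absence alone would not be a finding. What remains is that the Abstract, the sample size and the analysis section all rest on the omnibus test, which does not match the aim.
- **Change-score ANOVA is unbiased under randomisation.** True. The ANCOVA gain is one of precision and is secondary here.

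**Conclusion.** The concern holds in this form: the between-group test and sizing basis do not answer the stated aim, and the better-suited adjusted model is planned without being made decisive. At f = 0.4 and 20 evaluable per arm, about 78% of trials give a significant F whatever the order of the arms. The share that supports the combination over both single treatments ranges from about 62% down to zero, depending on that order.

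These figures assume that 0.4 is Cohen's f, and they assume normal outcomes with equal variances, 20% loss in each arm and no gain from covariates. The mismatch with the aim does not depend on them. The gap between alpha 0.15 and 0.05 is a separate matter; it enters here only because the calculations use the analysis level.

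**What to change.** For sputum viscosity, the outcome on which the trial is sized:

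1. Name one primary analysis: ANCOVA of the 1-week value on arm, baseline viscosity and severity stratum.
2. Name two planned contrasts, combination against breathing technique and combination against phonophoresis, each at two-sided 0.05.
3. Claim superiority over both single treatments only if both contrasts are significant. That claim needs no split of alpha. A claim resting on one contrast alone would need its own multiplicity rule.
4. Make the omnibus ANOVA and any model with further covariates supportive, with the covariates listed in full.
5. Do not select the model by a normality test on the trial data. If viscosity is known in advance to be skewed, specify a log transformation beforehand.

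**Cost.** No new data are needed: viscosity is measured at baseline and 1 week, and severity is known at randomisation. The power statement must change, however. Before any gain from baseline adjustment, 20 evaluable per arm give about 75% power per contrast and 62% for both if the combination is 0.85 SD better than two equal controls. With evenly spaced means, power for both is about 32%. The stated 90% does not apply to this criterion and should be restated. Keeping 90% per contrast in the favourable pattern would take 113 patients instead of 75. The article lists several primary outcomes, and this change does not settle how the others are to be ranked.

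### Filling missing outcomes with one undefined mean either shrinks the arm difference or raises the false-positive rate, and the stated sensitivity check does not re-estimate that difference

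*Protocol article*

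**What the plan says.** All of the following is in the protocol article.

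- *Data collection, management, and analysis*: the analysis follows intention to treat and will "use the sequence mean method to deal with the missing data to analyze the results of the comparison between groups of each outcome". No other method for missing data is named, and the term is not defined further.
- Same section, on sensitivity: "we will compare participants who did not complete the intervention with those who completed the intervention to verify the sensitivity of the results".
- Same section, on the test: "Inter-group differences between baseline and post-intervention among the outcomes will be compared by one-way analysis of variance". A general linear or generalized linear model adjusted for covariates and baseline follows. On the threshold: "A two-tailed *p*-value of < 0.05 will be taken as significant".
- *Sample size*: the plan assumes that "the dropout rate of our trial will be about 20% after the week-long intervention", and "the total sample size was 75, with 25 patients in each of the three groups".
- *Discussion*: losses of 10% to 18.75% are reported from two cited trials, but dropout here is expected to be lower because the patients are in hospital.
- *Monitoring of adverse events*: a participant with an adverse event or worsening disease is withdrawn at once, and the analysis uses whatever data exist.

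**The concern.** A single mean put in place of a missing value is treated as if it had been observed. What goes wrong depends on which mean is used, and the article leaves that open.

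- **All-arm mean.** Dropouts in every arm receive the same value, so the arm means are pulled together and the estimated effect is too small.
- **Own-arm mean.** The arm means do not move, but the filled values add sample size without adding spread. Standard errors are too small and the test rejects too often.

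The rule covers the between-group comparison of each outcome, the primary outcomes included. The only check on it contrasts two kinds of patient. It may show that dropouts differ at baseline, but it does not give the arm difference under another assumption about the missing values. Where a non-completer's 1-week outcome is missing, only the filled value is left to compare.

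Withdrawal for an adverse event or worsening may also link missingness to outcome. The article does not explain how analysing the available data in those patients fits with the mean fill.

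**Working it through.** **Inputs from the article.** Three arms of 25; 20% dropout; one-way ANOVA at two-sided 0.05; effect size 0.4, read as Cohen's f.

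**Assumptions of this check.** SD 1, normal data, values missing completely at random, and one arm differing from the other two.

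**1. The plan's own figure.** The article states: "We will have 90% power at the significance level (alpha) of 0.15 with an effect size of 0.4". With three arms and noncentrality N × f², 20 per arm gives power 0.905 at alpha 0.15. So N = 60, and 60/0.8 = 75, as stated. The 20% loss is therefore built into the sample size. (Alpha is 0.15 in the sample size and 0.05 in the analysis; that is a separate matter.)

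**2. The effect in SD units.** For means (d, 0, 0) the SD of the means is d√2/3. Setting this to 0.4 gives d = 0.4 × 3/√2 = 0.849 SD.

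**3. All-arm mean, 5 of 25 missing per arm.** Each filled arm mean is 0.8 × (observed arm mean) + 0.2 × (overall mean). The overall mean cancels in a difference, so the estimate is 0.8 × 0.849 = 0.679 SD, which is 20% too small.

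**4. Own-arm mean, 5 of 25 missing per arm.** The difference is unchanged. The within-arm sum of squares still has 57 degrees of freedom, but it is divided by 72, and each arm is counted as 25 rather than 20.
- The F statistic is inflated by (25/20) × (72/57) = 1.579.
- The 5% critical value of F(2, 72) is 3.124, and 3.124/1.579 = 1.978.
- With 2 numerator degrees of freedom, P(F(2, 57) > x) = (1 + 2x/57)^(−28.5). At x = 1.978 this is 0.148.

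**5. Simulation of the same cases, with the analysed variable filled.**

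| Missing per arm | Method | Type I error | Estimate (true 0.849) | Power at 0.849 |
|---|---|---|---|---|
| 5, 5, 5 | Complete cases | 0.051 | 0.850 | 0.78 |
| 5, 5, 5 | All-arm mean | 0.050 | 0.679 | 0.78 |
| 5, 5, 5 | Own-arm mean | 0.147 | 0.848 | not valid |
| 2, 3, 2 | All-arm mean | 0.050 | 0.770 | 0.84 |
| 2, 3, 2 | Own-arm mean | 0.085 | 0.850 | not valid |
| 8, 4, 3 | All-arm mean | 0.050 | 0.615 | 0.70 (complete cases 0.73) |
| 8, 4, 3 | Own-arm mean | 0.151 | 0.848 | not valid |

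Coverage of the 95% interval at 5 missing per arm, with the 0.849 SD difference present, is 95% for complete cases, about 90% for the all-arm mean and about 88% for the own-arm mean.

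**6. Only the 1-week value filled, then the observed baseline subtracted.** The filled changes now vary, so less variance is lost. This was simulated with equal SDs at both times and assumed baseline-to-1-week correlations of 0.3 to 0.7.
- Own-arm mean, 5 missing per arm: type I error about 0.09, coverage about 92%.
- Own-arm mean, 2 missing per arm: type I error about 0.06.
- All-arm mean, 5 missing per arm: type I error 0.05, the same 20% shrinkage, and power of about 0.6 to 0.7 against 0.78 for complete cases.

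**7. Lower loss.** Two missing per arm (6/75 = 8%) shrinks the difference by 8% under the all-arm mean. Losses of 2, 3 and 2 (7/75, about 9%) shrink it by about 9%.

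**The case against.** The case on the other side has several parts.

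- **The two harms exclude each other.** This stands. A reader might infer that the rule gives both biased effects and excess false positives. It does not: under random missingness the own-arm mean is unbiased, and the all-arm mean keeps type I error at 0.05. The term reads more naturally as the mean of the whole series, and on that reading the harm is attenuation.
- **The 0.15 error rate is conditional.** This stands. It needs an own-arm mean and a fill applied to the analysed variable. Filling only the 1-week value gives about 0.09. The covariate-adjusted model was not simulated.
- **Dropout may be low.** This stands in part. The *Discussion* expects it, but *Sample size* plans for about 20%. At about 10% the harm is smaller and still present.
- **Withdrawn patients.** A reader might infer that those withdrawn for worsening will be given an average outcome. The article does not establish this; *Monitoring of adverse events* may mean that data collected before withdrawal are used. No outcome-related missingness was simulated.
- **The sensitivity sentence may be shorthand** for comparing completer and intention-to-treat results. That is possible in a condensed article, but as worded it compares participants.
- **An analysis plan could define the mean.** It could, but neither definition makes the method sound.

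**Conclusion.** The concern holds. The article commits to one method for missing data, and on either reading that method does worse than complete cases under the mildest form of missingness.

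- **All-arm mean:** at the planned 20% loss the arm difference is about 20% too small, with coverage of about 90% and nominal type I error.
- **Own-arm mean:** the difference is unbiased, but type I error is about 0.09 to 0.15, depending on what is filled.
- **At about 10% loss:** 8 to 9% shrinkage, or type I error of about 0.06 to 0.085.

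These sizes rest on normal data missing completely at random, the assumed pattern of means and, for the change analysis, the assumed correlations. If withdrawal depends on outcome, further bias is possible and is not quantified here. The completer comparison, as worded, would show neither the shrinkage nor the inflation.

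**What to change.** In *Data collection, management, and analysis*:

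1. Delete the sequence-mean fill.
2. For outcomes with baseline and 1-week values, use a baseline-adjusted likelihood-based model, or multiple imputation that includes arm, baseline value and disease severity. Keep the covariate set small: with about 20 observed patients per arm, separate imputation within each arm on many covariates may be unstable.
3. For outcomes collected once, such as self-satisfaction, cooperation and length of stay, use multiple imputation or available cases.
4. Add to the completer comparison, or put in its place, a sensitivity analysis that re-estimates the arm contrast. Complete cases and a delta-adjusted analysis that gives missing patients worse outcomes are suitable; other choices would also serve.
5. Reconcile this section with *Monitoring of adverse events*: state which data from withdrawn participants enter the analysis and how their missing 1-week values are handled.

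The cost is revised wording, slightly more analysis work and somewhat wider intervals. No new data are needed.

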### Monitoring of adverse events

All adverse events that occur in our intervention will be monitored by researchers who are not involved in the data collection and have no conflicts of interest in terms of the data monitoring committee (DMC). Adverse events are defined as any untoward occurrences in study participants that are potentially related to the implementation of the study protocol. When a participant experiences an adverse event or a worsening of the disease, they will be immediately withdrawn from the trial, and statistical analysis will be performed with the existing data. The Ethics Committee will hold an annual meeting to monitor the execution of the entire trial.

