## Abstract

**Background:**

Chronic obstructive pulmonary disease (COPD) is a chronic inflammatory lung disease characterized by coughing, the production of excess sputum, and dyspnea. Patients with excessively thick sputum may have frequent attacks or develop more serious disease. The guidelines recommend airway clearance for patients with excessive sputum who are hospitalized with COPD. The active cycle of breathing technique is the most common non-pharmacological airway clearance technique used by physiotherapists. However, the effectiveness of the technique is not always guaranteed. Active cycle of breathing techniques require the initial dilution of the sputum, usually by inhalation drugs, which may have limited effects. Recent studies have found that phonophoresis decreases inflammation, suggesting the potential of the combined usage of active cycle of breathing techniques and phonophoresis. Therefore, the aim of this study is to explore the effectiveness and safety of combining active cycle of breathing technique and phonophoresis in treating COPD patients.

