### Ethics and dissemination

There is no anticipated harm and will be no compensation for trial participation. Research reports will be disseminated through scientific forums, including peer-reviewed publications and presentations at national and international conferences. The datasets analyzed during the current study will be available from the corresponding author on reasonable request.

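### Adverse events are defined by potential relation to the protocol, so harms thought unrelated go uncounted although safety is a stated aim

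*Protocol article*

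**What the plan says.** All of this is in the protocol article.

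- **Definition** (Monitoring of adverse events): "Adverse events are defined as any untoward occurrences in study participants that are potentially related to the implementation of the study protocol".
- **Aim** (Abstract, Background): "the aim of this study is to explore the effectiveness and safety of combining active cycle of breathing technique and phonophoresis".
- **Blinding** (Randomization, blinding, and allocation concealment): "neither the intervention practitioner nor the participant can be blinded to the treatment plan", "so blinding is only applicable for the data collection and evaluation".
- **Who monitors** (Monitoring of adverse events): events are "monitored by researchers who are not involved in the data collection", who also have no conflicts of interest. Whether they are blinded is not stated.
- **Consequence of an event** (same section): "When a participant experiences an adverse event or a worsening of the disease, they will be immediately withdrawn from the trial".
- **Expected harm** (Ethics and dissemination): "There is no anticipated harm and will be no compensation for trial participation". The intervention-group section nevertheless names skin burns and intolerance as reasons to stop phonophoresis.

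No section provides for recording untoward occurrences whatever their cause. Safety is not among the primary, secondary or additional secondary outcomes.

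**The concern.** The definition merges two questions that are normally kept apart: did something untoward happen, and was it caused by the study? Under this text the second must be answered before the first can be counted. The authors report that the combination has not been described in COPD, so there is little basis for deciding in advance which occurrences are related.

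Two things are at stake. First, an unexpected harm may be put down to the disease or to usual care and never enter the count. An analysis plan cannot recover events that were not collected. Second, if the tendency to call an event related differs between arms, the count by arm no longer reflects randomisation alone. That is plausible here. The people delivering and receiving treatment know the arm, and the only harms named in advance belong to phonophoresis. The breathing-only arm receives an inhaled mucolytic, which resembles the centre's usual care, so a reaction there may be credited to usual care.

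Because an adverse event also leads to withdrawal, uneven attribution could change who is withdrawn, and with that the missing efficacy data that are to be filled by mean substitution.

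**Working it through.** **1. Number at risk per arm.** The article gives no safety figure; its only relevant number is the sample size. Inputs from Sample size: three arms, effect size 0.4 (taken as Cohen's f), alpha 0.15, power 90%, dropout 20%. In a one-way ANOVA with 20 per arm (N = 60), the noncentrality is N × f² = 60 × 0.16 = 9.6 and the power is 0.905. Then 60 / (1 − 0.20) = 75, or 25 per arm, which matches the article. The point below does not depend on this figure beyond the 25 per arm.

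**2. What the condition does.** Let p be the true proportion of patients with an untoward occurrence and q the share called related. Then:

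- recorded proportion = p × q;
- recorded ratio of arm A to arm B = (p_A × q_A) / (p_B × q_B).

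If p is equal in both arms, the recorded ratio is q_A / q_B, which is attribution alone. If q is equal, the ratio is right but the counts are too small.

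**3. Illustration.** Every p and q below is an assumption; none is in the documents. There are 25 patients per arm. The last columns give the chance of a two-sided Fisher test below 0.05, by exact binomial enumeration.

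| True p (A v B) | Share called related (A v B) | Recorded | Expected counts, all → related | P(sig.), all events | P(sig.), related only |
|---|---|---|---|---|---|
| 20% v 20% | 90% v 30% | 18% v 6% | 5 v 5 → 4.5 v 1.5 | 0.022 | 0.119 |
| 30% v 30% | 90% v 30% | 27% v 9% | 7.5 v 7.5 → 6.75 v 2.25 | 0.023 | 0.263 |
| 30% v 30% | 80% v 40% | 24% v 12% | 7.5 v 7.5 → 6 v 3 | 0.023 | 0.114 |
| 40% v 20% | 40% v 80% | 16% v 16% | 10 v 5 → 4 v 4 | 0.231 | 0.020 |
| 30% v 30% | 60% v 60% | 18% v 18% | 7.5 v 7.5 → 4.5 v 4.5 | 0.023 | 0.022 |

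The first three rows show a difference created where none exists, and the fourth shows a real one hidden. In the last row attribution is equal: there is no false difference, but 40% of events are lost from both arms.

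**4. Link to withdrawal.** If the definition were widened and the withdrawal sentence left as it is, every occurrence of any cause would become a withdrawal. At an assumed 20%, that is 0.20 × 25 = 5 patients per arm. The dropout allowance is 25 − 20 = 5 per arm, so it would be used up entirely.

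**The case against.** The case against has real substance.

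- **The threshold is low.** Potential relation to the whole protocol is a wide net, and it covers the breathing exercise and the inhaled drug as well as the device. The text names no one who makes the judgement. This stands: the condition may exclude few events.
- **Monitoring is independent.** The monitors are outside data collection and free of conflicts. That is a safeguard, but independence is not blinding, and their blinding is not stated.
- **Worsening disease is named separately.** It triggers withdrawal, so it is not wholly lost. Oxygen saturation, spirometry and the COPD Assessment Test are also measured in every arm by blinded assessors. This stands, but worsening is not counted as an adverse event, and measurements at baseline and one week are not an event record.
- **Safety has limited weight in the article.** It appears in the abstract's aim but not in the aim at the end of the Introduction or the purpose in the Discussion, and no between-arm event comparison is stated.
- **This is a condensed article.** Recording fields and tabulation may be in the case report form or full protocol. That answers a complaint about missing detail. It does not answer one about a definition that is stated.

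A reader might infer that the trial's safety comparison is biased against phonophoresis by a known amount, or that every comparison is affected. The documents support neither. They contain no event rates or attribution shares. Attribution to the device would act alike in the combined and phonophoresis-only arms, so that comparison is largely untouched. Nor is the trial open-label throughout: outcome assessment is blinded.

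**Conclusion.** The point holds as one of definition. Following the stated rule leaves untoward occurrences thought unrelated uncounted, in a trial that gives safety as an aim and studies a combination its authors believe to be unreported in COPD. That loss does not depend on any difference between arms.

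Distortion between the phonophoresis arms and the breathing-only arm is possible but conditional: it needs attribution that differs by arm. Unblinded practitioners and participants, and monitors whose blinding is not stated, make this plausible; nothing in the documents shows that it will happen or how large it would be. The figures in the working show mechanism and direction only. The point is worth correcting before the safety results are relied on. It does not affect the sample size.

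**What to change.** In Monitoring of adverse events:

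1. Define the events to be recorded as every untoward occurrence in all three arms, regardless of presumed cause.
2. Record relatedness as a separate field, preferably rated by someone blinded to arm.
3. Report both all-cause and related events by randomised arm.

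The same section makes an adverse event a trigger for immediate withdrawal. The wider recording definition must not automatically widen that trigger, so the two sentences have to be separated and reconciled by the investigators. What the withdrawal rule should be is a clinical matter on which this review takes no position.

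The cost is somewhat more recording during a one-week inpatient stay and a longer event list. Counts of related events remain available, and N stays at 75.
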